|  | 5d | [name]. [name], Clinic for Internal Medicine I, Ulm (Study leader, Protocol Committee)  [name]. [name], Institute of Medical Systems Biology, Ulm (Study leader, Protocol Committee)  Dr. med. [name], Clinic for Internal Medicine I, Ulm (Study coordinator, Protocol Committee)  [name], Comprehensive cancer centere Ulm (trusted third party)  [name], Institute of Medical Systems Biology, Ulm (Statistic and biometry)  M.sc. [name], Institute of Medical System Biology (Protocol Commiteee)  [name], Institute of Medical System Biology (Protocol Commiteee)  M.sc. [name], Institute of Medical System Biology (Protocol Commiteee)  M.sc. [name], Institute of Medical System Biology (Protocol Commiteee)  [name] [name], Institute of Medical System Biology (Protocol Commiteee)  [name] [name], Institute of Medical System Biology (Protocol Commiteee)  [name], Ulm University Clinic (Protocol Commiteee) |
| Introduction |  |  |
| Background and rationale | 6a | Due to the respective tumor therapy protocols, but also due to limited resources, doctors only see their outpatients at certain intervals. Patients often forget important information about side effects, intolerances and general well-being or do not consider this information relevant.  In particular, drug combination therapies in oncology often contain active ingredients that can cause side effects such as nausea, inflammation of the mucous membrane (mucositis), diarrhea (diarrhea) or polyneuropathy. The acceptance of tumor therapy is decisively determined by the occurrence and duration of the side effects. If the therapy is well tolerated by the reduction of side effects, an improvement in quality of life is achieved. This is an important goal of a tumor therapy that also takes into account the psycho-oncological and social needs of the patients.  For the standardized documentation of possible relevant side effects and other therapy-associated information, an app has been developed to make it easier for patients to record these side effects.  In a first part, the acceptance and applicability of the app will be tested within the scope of the present study. If this first part is completed with positive results, a second phase is planned to investigate the effect of using the app on the management of side effects and their supportive therapy, as well as the maintenance of the original chemotherapy dose. |
|  | 6b | We examine the impact of new documentation media. Therefore, we compare a group of patients who report the occurred adverse events via the NEMO smartphone app and patients using standard reporting procedure. |
| Objectives | 7 | Patient acceptance of a new means of communication, Reduction of side effects by at least 1 degree according to CTCAE at study start. |
| Trial design | 8 | This study will be implemented in two parts. The first part should evaluate the feasibility and acceptance of a smartphone-based adverse reaction documentation. It will be followed by a second part. which will compare the impact of smartphone reported adverse events regarding applied therapy doses to those of patient with standard care. For the detection of occurred adverse events at an early stage, the participants will answer a standardized questionnaire (Table 1 and 2) via the NEMO app every day. Depending on the underlying therapy scheme, the NEMO questionnaire can be selected for chemotherapy (Table 1) or combined immunotherapy (Table 2), targeted therapy, and chemotherapy. NEMO allows for switching the therapeutic settings in case the therapeutic scheme changes. During therapy sessions, the documented data is transmitted securely via QR-codes to the treating physician and used for future therapy settings. To assess the. feasibility, 30 patients will be divided non-randomly into three age groups (< 55 years, 55-75 years, >75 years) of 10 patients each. These people will be followed over six months. Participants will answer the respective NEMO questionnaire about adverse events on a daily basis over these six months. After six months, they will answer a questionnaire about user-friendliness and feasibility (Table 3). Evaluation of these questionnaires allows for studying the different patients' characters and their potential benefit of using NEMO. The answered questionnaires could also give insights to identify barriers to answering the questions. The results of this evaluation enable us to amend the criteria for recruiting patients of the second part, such as their age and improving the application for the second part of the study. To assess the reduction of adverse events, 36 participants will be randomly assigned a group of 18 persons (smartphone user and standard care). Again, smartphone users will answer their respective NEMO questionnaires every day about occurred adverse events for six months. The transfer of their reported data takes place every second month in parallel with the reevaluation of tumor therapy. Participants of the standard care group will report their occurred adverse events and duration only during their personal appointments. What the patient remembers and reports depends on each participant and is very individual. Based on these reported adverse events, physicians will delineate a CTCAE scoring. Physicians will additionally fill out an electronic case report form containing tumor stage and information about therapeutic substances and doses. Moreover, patients of both study arms will answer a questionnaire about life quality which is based on the European Organization for Research and Treatment of Cancer (EORTC) questionnaire at enrolment and once at the end of the study to investigate whether NEMO can improve the quality of life. |
| Methods: Participants, interventions, and outcomes | | |
| Study setting | 9 | Study will be conducted at the University Hospital Ulm |
| Eligibility criteria | 10 | Inclusion Criteria:   - infusional combination therapy with at least two chemotherapy substances with or without further targeted therapies - combination of at least two immune-checkpoint inhibitors - able to read and understand German   Exclusion Criteria:  Participants who meet any of the following criteria will be excluded:   - severe neurological disorders   severe psychiatric disorders |
| Interventions | 11a | Not applicable. The study is to analyse the potential of new media for documentation. This can be considered as observational study. |
|  | 11b | Criteria for discontinuing are death, leaving Ulm or acquiring of exclusion criteria. |
|  | 11c | NEMO provides a user friendly interface for elderly individuals (clear design, big fonts, and auditory feedback) helping an easy fill in of questionnaires. |
|  | 11d | There are no interventions that are permitted or prohibited during the trial. |
| Outcomes | 12 | Primary Outcome:  Patient acceptance of a new medium of communication  Change of occurred adverse events  Secondary Outcome:  Maintenance of chemotherapy doses through better adverse event management  Change in the quality of life |
| Participant timeline | 13 | Both parts of the study are planned to last 6 months and build on each other (see Fig 1 and Table 4). |
| Sample size | 14 | Sample size was determined with the statistical software G*Power (v3.1.9.4) We assumed an effect size of 1, corresponding to a side effect variation of 1 on the Likert scale, a type I error rate = 0.05, and a power of 80%. Planning for a Mann-Whitney test comparing the difference between two groups led to a required sample size of 18 individuals per group (Fig 2). |
| Recruitment | 15 | The first part will be used to assed the right group of subjected that later on will allow random assignment in the second part of the study. |
| **Methods: Assignment of interventions (for controlled trials)** | | |
| Allocation: |  |  |
| Sequence generation | 16a | The physician's desktop application belonging to the app provides the pseudonym NEMO-Identifier for the participating test person. This is an isolated system that is independent of the smartphone app. |
| Allocation concealment mechanism | 16b | Method of random allocation of patient will be set in at the time of the beginning of the study. |
| Implementation | 16c | The study coordinator will take care of assigning patients to random allocation into the two groups. |
| Blinding (masking) | 17a | Patients and physicians will be aware of the allocation. Given the rational of the study, no blinding is required. Committee members in charge of data analysis will only receive pseudonymised patient data. |
|  | 17b | No blinding is required. |
| **Methods: Data collection, management, and analysis** | | |
| Data collection methods | 18a | For the daily recording of occurring side effects, participants fill out a questionnaire on their smartphones (Tables 1 and 2). This collected data can be transferred to the desktop application of the treating physician by means of QR code, where a visual representation of the logged side effects is displayed.  No personal data is stored in the app itself. Here, data on pain, food intake and well-being are queried and stored with the respective CTCAE score.  The corresponding desktop application of the physician records the master data (surname, first name and date of birth) of the test person as well as the side effect scores transmitted by the test person.  For the evaluation of the app or the quality of life, additional paper questionnaires (EORTC-QLQ-C30) are answered by the participants in handwriting with ballpoint pens. Clinical data are documented by the treating physician using data sheets of the electronic Case Report Form. |
|  | 18b | We set up in NEMO reminders for the patients in order to minimize potential missing data points and increase compliance. |
| Data management | 19 | smartphone app runs exclusively offline and consequently avoids transmission over potentially insecure internet connections to store data on remote servers. Information is passed to physicians via QR code systems. |
| Statistical methods | 20a | Wilcoxon-Mann-Whitney test will be used to assess known-groups validity, as well as to compare differences between NEMO users and patients with standard reporting procedure concerning the severity of occurred adverse events. NEMO uses a Likert scale to score each questionnaire item. To rate the overall effect of adverse event management, a summary score will be calculated from a weighted sum of questionnaire items by the maximum number of items. Spearman correlation will be used to evaluate convergent validity between each item and the summary score of the quality of life questionnaire or its symptom scales. The impact of the side effect management will be analyzed by comparing changes in an item's scoring between the reevaluation steps during tumor therapy. This comparison will be made using a Jonckheere-Terpstra test |
|  | 20b | All statistical details have been given. |
|  | 20c | We set up in NEMO reminders for the patients in order to minimize potential missing data points. |
| **Methods: Monitoring** | | |
| Data monitoring | 21a | Members of the protocol committee and biometry and statistical analysis will be in charge of monitoring the pseudonymised data. Statical approach for analysis is described above in section 20a-c. |
|  | 21b | For exclusion we refer to 10c. Interim data will be accessed by the committee described in 21a. Study leaders and coordinator will be in charge of deciding for study termination. |
| Harms | 22 | Not applicable to the trial. The aim of the trial is to assess new media communication for report and reduction of adverse events. |
| Auditing | 23 | Not applicable to the trial. |
| Ethics and dissemination | | |
| Research ethics approval | 24 | Consent was obtained in a written form by the ethics committee Ulm University, Ulm, Germany - Proposal no. 406/19. |
| Protocol amendments | 25 | All relevant involved parties will be informed of important protocol modifications. |
| Consent or assent | 26a | All patients will have to sign a written declaration of consent in order to participate to the study. All participants will be informed of procedure and endpoint. They will be also given the possibility to ask questions to coordinators before consenting to take part to the study. Also, possibility of withdrawing consent at any time is an option. |
|  | 26b | This point is not applicable to the study. No biological specimens will be taken. |
| Confidentiality | 27 | Patients data will be passed to clinicians in offline modality and through QR code. |
| Declaration of interests | 28 | No competing interests for principal investigators is declared. |
| Access to data | 29 | In the study phase, the desktop application, which stores all master data of the test persons on a computer that is protected against access, is the data storage. In a later phase, a login system for the desktop application will be set up. It is planned to integrate the application into the hospital's clinical information system to ensure legally compliant documentation and data protection of personal data according to the applicable standards. Technical staff of the project will only receive data in pseudonymized form. Thus, it is not possible for these employees to draw conclusions about individual persons.  For the evaluation of the study, the data is transferred to the Trusted Third Party, pseudonymized and released for analysis. Additionally, the Trusted Third Party checks the plausibility of the data (monitoring). |
| Ancillary and post-trial care | 30 | The study has an observatory nature. No drugs or treatments will be provided, and therefore potential harm to participants is not possible. |
| Dissemination policy | 31a | After evaluation of the data, a prompt and speedy publication of the results is planned. There will be a publication to answer the main question (regardless of the results). |
|  | 31b | As authors are involved: The study committee as well as the principal investigators of the study center, who contributed significantly to the recruitment by including more than 10% of the total number of study participants. Additional authors will be included for evaluation or manuscript preparation according to their scientific input. |
|  | 31c | Study protocol is planned to be published under open access. |
| Appendices |  |  |
| Informed consent materials | 32 | Figure 1: Trial design  Figure 2: Sample size estimation  Table 1: Smartphone questionnaire chemotherapy  Table 2: Smartphone questionnaire immunotherapy  Table 3: Feasibility questionnaire  Table 4: Flow chart of study procedure |
| Biological specimens | 33 | No biological specimens will be used in the trial. |

Figure 1: Trial design

Figure 2: Sample size estimation

Table 1: Smartphone questionnaire chemotherapy

Table 2: Smartphone questionnaire immunotherapy

Table 3: Feasibility questionnaire

Table 4: Flow chart of study procedure

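### Part 1 describes acceptance only by a questionnaire at six months, with no exit questionnaire or usage measure, so acceptance is likely, though not certain, to be overstated and barriers may be missed

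*Protocol*

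**What the plan says.** **Role of acceptance.** Item 12 lists "Patient acceptance of a new medium of communication" first among the primary outcomes. Item 6a makes the continuation of the study depend on Part 1: "If this first part is completed with positive results, a second phase is planned". Item 8 adds that the Part 1 results "enable us to amend the criteria for recruiting patients of the second part, such as their age", and item 15 says that Part 1 serves to identify the right group for Part 2.

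**Measurement.** Item 8 states that "30 patients will be divided non-randomly into three age groups (< 55 years, 55-75 years, >75 years) of 10 patients each" and that "These people will be followed over six months", with daily entries in the app. Then: "After six months, they will answer a questionnaire about user-friendliness and feasibility (Table 3". No other administration of this questionnaire is described. Item 8 expects the completed questionnaires to show barriers to use as well.

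**Ways to leave early.** Item 11b: "Criteria for discontinuing are death, leaving Ulm or acquiring of exclusion criteria". Item 26a: "possibility of withdrawing consent at any time is an option". Neither item mentions a questionnaire at exit.

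**Data from the app.** Patients record side effects daily, and the entries reach the physician by QR code at therapy sessions (items 8, 18a and 19). Reminders in the app are the only measure named against missing data (items 18b and 20c). The text does not link the record of entries to acceptance.

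**The concern.** A single questionnaire at the end of follow-up collects the views of those who are still there. These patients receive combination chemotherapy or combined checkpoint inhibitors and are asked for an entry every day for six months. The protocol itself foresees death, relocation, acquired exclusion criteria and withdrawal. A patient who withdraws because the app is a burden is the most informative witness about non-acceptance, and has no described way to say so. A patient who stops using the app early but remains in the study may be asked months after the experience.

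Two uses of Part 1 are exposed. The acceptance figure that supports the decision on Part 2 may look better than it is. The barriers that Part 1 is meant to find, and that may shape the recruitment criteria and the revision of the app, may go unrecorded. With 10 patients per age group, two or three lost patients are enough to move a group's figure materially.

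The timing of the questionnaire is a data-collection decision. An analysis plan can choose a denominator later, but it cannot recover answers that were never asked for.

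**Working it through.** **The plan's own figures.** Part 1's 30 patients come without a calculation, an assumed acceptance rate or an assumed loss rate, so there is nothing to reproduce for this point. The one calculated figure, 18 per group in item 14, concerns Part 2. It does reproduce (Mann-Whitney test, effect size 1, two-sided 0.05, normal-parent efficiency 3/π, power 81.2%), but it has no bearing here.

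**Inputs.** From the protocol: N = 30, or 10 per age group (item 8). Assumed, because the protocol gives neither: the acceptance rate *r* among those who answer at six months, and the share *d* who do not answer. Acceptance is treated as yes/no for illustration only; the visible text does not define a score.

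**Formula.** Let *a* be the unknown acceptance rate among those lost.

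- Acceptance among all enrolled = r(1 − d) + a·d
- Responder rate minus enrolled rate = d(r − a)

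The responder rate is too high if a < r, correct if a = r and too low if a > r. Setting a = 0 and a = 1 gives the bounds r(1 − d) and r(1 − d) + d.

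**One age group, 3 of 10 lost, 6 of 7 responders positive (assumed).**

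- Responders: 6/7 = 86%
- All lost counted as not accepting: 6/10 = 60%
- All lost counted as accepting: (6 + 3)/10 = 90%

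**All 30 patients, 9 lost, 17 of 21 responders positive (assumed).**

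- Responders: 17/21 = 81%
- Lower bound: 17/30 = 57%
- Upper bound: (17 + 9)/30 = 87%

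**Range over the loss rate, with r = 80% (assumed).**

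| Share lost, d | Lower bound, 0.8(1 − d) | Upper bound, 0.8(1 − d) + d | Largest overstatement, 0.8d | Largest understatement, 0.2d |
|---|---|---|---|---|
| 10% | 72% | 82% | 8 points | 2 points |
| 20% | 64% | 84% | 16 points | 4 points |
| 30% | 56% | 86% | 24 points | 6 points |
| 40% | 48% | 88% | 32 points | 8 points |

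**Reading.** When most responders are positive there is far more room for overstatement than for understatement. Where the truth lies depends on *a*. Withdrawal because of the app pulls *a* down; death or moving away need not change it. The protocol as described would not supply the data to tell these apart.

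**The case against.** A reader might infer that every patient who stops using the app drops out of the acceptance figure. The protocol does not support that. Stopping the app is not among the discontinuation criteria in item 11b, and item 8 follows all 30 patients for six months and has them answer at the end. The evaluation questionnaires are on paper (item 18a), so someone who abandoned the app can still complete one. For these patients the weakness is late recall, not exclusion.

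A reader might also infer that acceptance is certainly overstated. That is not shown either. Death, relocation and a severe neurological or psychiatric disorder are not rejection of an app. Only withdrawal plausibly is, and no rate is given for it. The bounds above run in both directions, and no text restricts the analysis to completers. The denominator and the handling of non-responders may properly be set in an analysis plan that is not at hand.

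Three further points stand:

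- Figure 1 and Tables 3 and 4 are listed without their content, and item 13 refers to Figure 1 and Table 4 for the timeline, so an additional time point there cannot be excluded.
- Item 8 says that the results allow recruitment criteria to be amended. It does not make them decide mechanically which age groups enter Part 2, and it plans no test between age groups, so the low power of such a test is no argument here.
- Counting everyone without an answer as not accepting would score deaths and relocations as rejection. If these were more frequent in the oldest group (an assumption), that group would be penalised unfairly. The rule is usable only as a lower bound.

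None of this supplies answers from patients who leave before six months.

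**Conclusion.** The point holds as a weakness of data collection. As described, Part 1 obtains no acceptance or barrier information from patients who withdraw or are discontinued before six months, and only late, recalled information from those who stop the app but stay. Since withdrawal can reflect rejection of the app, upward bias in a primary outcome that conditions Part 2 is likely, though neither its size nor its direction can be fixed from the protocol.

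If a fifth to two fifths of patients were lost, an 80% rate among responders could correspond to as little as 64% to 48% of those enrolled, or to as much as 84% to 88%. These ranges rest on assumed loss and acceptance rates and on a yes/no reading of acceptance. The conclusion also assumes that the timeline figure and tables, which are not shown, contain no earlier or exit administration. It is a sensible and inexpensive improvement, not a flaw that invalidates the study.

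**What to change.** 1. In item 8, state that the Table 3 questionnaire is given at early withdrawal, at discontinuation where the patient is able, and when app use stops, as well as at six months. Record the reason each time. An exit answer stays voluntary for a patient who withdraws consent.
2. Report the share of study days with a completed NEMO entry for all 30 enrolled patients, overall and by age group. Because the app works offline, use the data transferred by QR code and add a transfer at exit where possible; otherwise entries since the last transfer may be lost.
3. Report acceptance among responders together with the two bounds over all enrolled (non-responders counted as not accepting, then as accepting), with deaths and relocations shown separately. Do not use the lower bound as the main definition.
4. State that these figures will be considered in the decision on Part 2 and its recruitment criteria.

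**Cost.** A few sentences of protocol wording, some additional paper forms, and a QR transfer at exit. The reported acceptance may turn out lower.

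### Part 2 records adverse events by a daily app log in one arm and by recall at appointments in the other, so the primary comparison confounds capture with any effect of NEMO.

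*Protocol*

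**What the plan says.** The relevant statements are all in the protocol.

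- **Aim.** Item 7 (Objectives) includes "Reduction of side effects by at least 1 degree according to CTCAE at study start". Item 12 lists change in adverse events as a primary outcome.
- **NEMO arm.** Item 8 (Trial design): "smartphone users will answer their respective NEMO questionnaires every day about occurred adverse events for six months". Items 18b and 20c add reminders to limit missing entries. Item 18a says the app data are "queried and stored with the respective CTCAE score".
- **Control arm.** Item 8: "Participants of the standard care group will report their occurred adverse events and duration only during their personal appointments". The next sentence adds: "What the patient remembers and reports depends on each participant and is very individual".
- **Grading.** Item 8 says physicians derive a CTCAE score from the reported events. Item 17a says patients and physicians know the allocation.
- **Test.** Item 20a uses the Wilcoxon-Mann-Whitney test to "compare differences between NEMO users and patients with standard reporting procedure concerning the severity of occurred adverse events".
- **Sample size.** Item 14 plans 18 per group for an effect size of 1, equated with one point on the Likert scale. Item 20a says NEMO scores its items on that scale.
- **Common instrument.** The only patient questionnaire described for both arms is the EORTC-based one, at enrolment and at the end, which serves a secondary outcome.

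**The concern.** For this outcome the intervention is also the measuring instrument, and in one arm only. The input to any severity score differs by arm in structure (fixed items against free report), in frequency (daily against per appointment) and in dependence on memory. Randomisation balances the patients but cannot balance this, because the difference is created after allocation.

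The protocol's own rationale (item 6a) is that patients often forget side effects or think them unimportant. On that premise some control events never enter the record. For a count or burden summary, NEMO would then tend to look worse than it is, and a real benefit could be hidden. For other summaries the distortion can vanish or reverse. In either case a significant result could not be attributed to NEMO, and a null result could not be read as no effect.

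The planning assumption has the same weakness. One Likert point is a difference on a scale that, as described, only the NEMO arm fills in.

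**Working it through.** **1. The plan's own figure.** Inputs from item 14: effect size d = 1, alpha 0.05 (taken as two-sided), power 80%, Mann-Whitney. Method: noncentral-t power with n multiplied by the asymptotic relative efficiency for a normal parent, 3/π = 0.955. Power is 78.8% at n = 17 and 81.2% at n = 18, so 18 per group is reproduced. The arithmetic is sound if capture is equal in both arms.

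**2. A constant offset.** Suppose control scores are under-recorded by b (assumed) in units of the planned 1 SD. The test then sees d = (true benefit) − b. With a true benefit of 1 and b = 0.5, the net d is 0.5 and power falls from 81% to 30% by the formula above. A simulation of 10,000 trials gives 80% falling to 28%.

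**3. An episode model with no true effect.** All inputs here are assumptions: Poisson episodes with mean 4 per two-month window; grades 1, 2 and 3 with probabilities 0.55, 0.30 and 0.15; 18 per arm; each arm records a fraction of its episodes.

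Hand check for total burden (sum of grades):

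- Mean at full capture: 4 × (0.55 + 2×0.30 + 3×0.15) = 4 × 1.60 = 6.4.
- Variance at full capture: 4 × (0.55 + 4×0.30 + 9×0.15) = 4 × 3.10 = 12.4. Both scale with the fraction captured.
- App 100%, control 70%: difference 6.4 − 4.48 = 1.92; SD = √((12.4 + 8.68)/2) = 3.25; d = 0.59; rejection about 39%.
- App 100%, control 50%: difference 3.2; SD = √((12.4 + 6.2)/2) = 3.05; d = 1.05; rejection about 85%.
- App 85%, control 70%: difference 5.44 − 4.48 = 0.96; SD = √((10.54 + 8.68)/2) = 3.10; d = 0.31; rejection about 14%.

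Simulated false rejection (10,000 trials, asymptotic Mann-Whitney; mean grade from 3,000 trials, taken over recorded episodes):

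| App / control capture | Total burden | Worst grade | Mean grade |
|---|---|---|---|
| 100% / 100% | 5% | 5% | 4% |
| 100% / 70% | 38% | 13% | 5% |
| 100% / 50% | 86% | 39% | 5% |
| 85% / 70% | 14% | 7% | 6% |

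The excess rejections on total burden and worst grade all go against NEMO.

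**4. Recall that depends on severity.** Assume controls recall 0.60, 0.80 and 0.95 of grade 1, 2 and 3 episodes, and the app captures all.

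- Overall recall: 0.55×0.60 + 0.30×0.80 + 0.15×0.95 = 0.7125.
- Mean recalled grade: (0.33 + 0.48 + 0.4275)/0.7125 = 1.74, against a true 1.60. Controls look 0.14 grade worse.
- Rejection on mean grade is about 12% (11% to 13% across runs), favouring NEMO. Worst grade rejects in about 6%. Total burden rejects in about 23%, against NEMO.

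The same recall pattern therefore gives opposite signs on two plausible summaries.

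**The case against.** **The medium is the intervention.** Item 6b presents the trial as a study of documentation media, so different recording is intended. That would suffice if the outcome were completeness of documentation. Items 7 and 12 make it a reduction or change in adverse events, so the objection does not remove the problem.

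**Change from baseline cancels it.** If each arm's capture rate were the same at baseline and follow-up, change scores would reject at about 5%. The protocol does not say how baseline is captured. A baseline taken before app use begins would lack the daily log in both arms, and the difference would then enter only at follow-up.

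**The same physician grades everyone.** A reader might infer from the CTCAE scores stored in the app that the rater differs by arm. The text does not settle this: the sentence on physician grading can cover both arms, since NEMO data also reach the physician. Even so, the grade rests on reports that differ by arm, and the grader is unblinded.

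**Timing.** A reader might see a contradiction between "During therapy sessions, the documented data is transmitted securely via QR-codes to the treating physician" and "The transfer of their reported data takes place every second month in parallel with the reevaluation of tumor therapy". The first stands in the general description of the app and the second in the account of Part 2, so they can coexist. Nothing here rests on them.

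**The size depends on harsh inputs.** This stands. Perfect app capture is unfavourable to the plan, and the protocol itself expects missing entries. The figures are a range, not an estimate.

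**Unseen tables.** Tables 1 to 4 are listed but their content is not in the text reviewed. Table 4 might show an assessment common to both arms, and should be checked first.

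**Conclusion.** The concern holds as confounding: as written, the Part 2 adverse-event comparison cannot separate how events are captured from what NEMO does. It is a fault of data collection. Events that controls never report cannot be recovered in analysis, and a larger sample does not remove the bias.

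Two stronger readings are not supported. One is that the comparison measures the recording method and not NEMO's effect; it mixes the two. The other is that NEMO must look worse; that follows for burden-type summaries if patients forget, but not in general, and unblinded reporting could push either way.

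Under the assumed inputs, false rejection runs from about 5% (mean grade, representative recall) to 86% (total burden, 50% recall), with about 12% in NEMO's favour in the severity-dependent case on mean grade. The protocol gives neither the recall loss nor a fixed between-arm severity summary, so no single figure should be quoted as the bias. The planned 18 per group is not in dispute under its own inputs.

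**What to change.** Base the between-arm adverse-event comparison on one instrument that both arms complete in the same way. There are two options.

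1. Give both arms the NEMO items (Table 1 or 2, by therapy) on paper, with the same look-back window, at enrolment and at each two-monthly re-evaluation. Have the form completed before the QR data are opened, and do not show it to the treating physician.
2. Use the QLQ-C30 symptom scales, already collected in both arms at enrolment and end, as the common between-arm measure.

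In either case, keep the daily app data for delivering the intervention and for within-arm description, and say so in item 20a.

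**Cost.** Option 1 needs about 36 patients × 4 visits = 144 short forms. The measure becomes recall-based in both arms. Daily loggers may still recall better on a look-back form, and a structured form may prompt controls to report more, so some imbalance or dilution could remain. Option 2 adds no forms, but it has only two time points and uses a scale other than the Likert point behind n = 18, so the sample-size assumption would have to be restated.
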